### Specific Aims

We are conducting research to gain greater insight into the biological mechanisms underlying epidemiologic evidence linking social relationships, stress, and cardiovascular health. Specifically, our experimental research examines the effects of exogenously administered (intranasal) oxytocin on psychological and physiological outcomes, under conditions of stress. The specific aims of this project are to test the following hypotheses:

1. Oxytocin ameliorates the deleterious neuroendocrine, cardiovascular, and subjective effects of stress.

2. Oxytocin and social support have similar and additive stress-buffering effects.

3. Effects of oxytocin are stronger in women versus men.

4. Effects of oxytocin are similar across a range of younger and older adult ages.

To test these hypotheses, we are conducting a placebo-controlled double blind study using a sample of healthy men and women recruited from the community. We are considering oxytocin effects on a range of outcomes. These include autonomic reactivity as measured by blood pressure responses and high frequency heart rate variability (measure of cardiac vagal tone). Stress-related cardiovascular phenotypes as characterized by the patterning of ventricle contractility, vascular resistance, and cardiac output will also be assessed. Other outcomes include measures of neuroendocrine effects as measured by levels of cortisol and dehydroepiandrosterone (DHEA), subjective distress and positive affect. Participants are randomly assigned to receive either exogenous oxytocin or placebo. They undergo a social stress manipulation with or without social support (randomly assigned), and outcome measures are obtained at multiple times during the experimental procedure. The experiment will test whether effects of oxytocin and social support are similar and additive, and will also compare effects of oxytocin and social support across adult men and women of varying ages.

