### Data Analyses

Analysis will begin with thorough descriptive and graphical examinations of variables in both studies, including comparisons across randomization groups. Analyses will include adjustment for covariates if not covered by randomization. Distributional assumptions of dependent variables will be assessed, and measures will be transformed, if necessary. Analyses will use applications of the general linear model as appropriate for each hypothesis under study. For example, when examining relations between the dichotomous factors of social support, oxytocin, and gender, we will use analyses of variance (ANOVA) with repeated measures. Responses are measured over time both before and after the stress induction. Cardiovascular outcomes will be considered both in separate models and using multivariate analysis of variance, as they are likely correlated within each individual. When considering the relation between age (a continuous factor) and oxytocin, we will use multiple linear regression techniques incorporating an interaction term between age and oxytocin as well as relevant covariates, but we will also consider using linear mixed models to account for the repeated measures on the outcomes and the resulting intra-individual correlation in these measures. Statistical tests will be two-tailed and conducted at the .05 level of significance. Regarding the specific hypotheses, this experimental study provides data for analyses that will examine whether:

1) Under conditions of stress, higher levels of oxytocin lead to higher vagal control, more benign stress reactivity (reduced blood pressures, cardiovascular response patterns characterized by increased ventricular contractility, heart rate, and cardiac output, but decreased total peripheral resistance), higher anabolic balance, and reduced subjective distress, by comparing the change in responses before and after stress across the oxytocin and placebo control groups.

2) Oxytocin combined with social support reduces the effects of stress more than the individual effects of oxytocin and social support by comparing the change in responses before and after stress across all possible combinations of the two treatment groups (oxytocin vs. placebo; social support vs. no social support). Oxytocin and social support combined is expected to be associated with highest levels of vagal control, the most benign pattern of autonomic reactivity, and the lowest levels of subjective distress.

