3) Oxytocin reduces effects of stress more for women than for men by comparing changes in responses before and after stress in the presence of oxytocin or placebo across men and women. Exploratory analyses will consider whether the strength of the effects of oxytocin may be attributable to differences in estrogen levels by comparing effects of oxytocin across pre- and post-menopausal women (estrogen levels are expected to be higher among pre-menopausal women) and also considering interactions between estrogen (measured directly via levels of estradiol) and oxytocin in both men and women.

4) Effects of oxytocin are similar across younger and older aged adults by comparing the change in responses before and after stress in the presence of oxytocin or placebo across age.

The general analytic strategy will start by fitting a model that includes all interactions and then move to a statistically equivalent simpler model using likelihood ratio tests. In cases where there are more than two measurements over time, several covariance structures will be considered. The possibility of multiplicative effects (between oxytocin and social support, for instance) will be explored graphically. Other research has suggested that the effects of oxytocin and/or social support may not emerge immediately. Thus, elapsed time will be an important consideration, and separate analyses will be conducted to determine when over the course of the experimental tasks, effects of oxytocin and/or social support are evident on cardiovascular, neuroendocrine, and subjective parameters. These analyses will involve multiple single comparisons between baseline and later levels of the dependent variables, and will be conducted with adjusted levels of significance as appropriate (e.g., t-tests with Bonferroni corrections).

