### Power and Sample Size

Power is calculated to accommodate both the effects of the dichotomous experimental factors, as well as age (measured as a continuous variable). Since power will be limited by hypotheses where 3-way interactions are being tested, power is first computed for representative outcomes for those hypotheses (including vagal tone measured by RSA), based on information available in the existing literature. Power for hypothesis 1 will be higher. Power is calculated for a two-sided test of a three-way interaction over ranges of reliabilities and differences to be detected. For all outcomes, 40 participants per gender/treatment group will result in power of 80-90% to detect effect sizes similar to those seen in the literature. Since participants are used as their own controls, power varies by measurement reliability, and this sensitivity was considered. Power was computed using a normal test that assumes independence across participants, compound symmetric covariance within each subject, and approximately constant variance before and after the treatment. Values for the parameters used here were obtained from the literature [72,88,89,98,128]. In addition, a sample of this size will provide 80% power to detect a medium sized effect using multiple linear regression to consider age and oxytocin adjusting for other covariates as necessary [129].

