### Future Directions

This research uses a multidisciplinary approach to examine neurobiological underpinnings for the observed epidemiological associations between positive social interactions and emotion experiences and physical health outcomes in older adulthood. Our study will systematically test a biobehavioral model of social relationships and health, and examine a key peptide that may underlie the observed beneficial effects of positive social interactions and psychological states on health and longevity. At conclusion of the study we will have solid evidence concerning the effects of oxytocin on stress response, whether it has similar effects regardless of age or gender, and whether its potency depends in part on circulating levels of estradiol. Further work can build on this knowledge and consider potential effects of oxytocin on other biological parameters such as levels of inflammation or catecholamines.

Future research should examine how effects of oxytocin may relate to effects of different types of social support (friend, same sex, stranger, etc), and whether oxytocin may actually promote provision of more support or greater receptiveness to all kinds of support. A greater understanding of how oxytocin functions in human health may also be obtained by identification of gene by environment interactions in relation to oxytocin, and by considering the relation between oxytocin, the opioid pathway and endogenous opioids.

This novel area of investigation has the potential to have major impact on understanding how positive social and emotional experiences influence adult stress response, health, and longevity. This research will provide a solid platform from which to launch a larger interdisciplinary research program aimed at identifying neurobiological underpinnings for the observed epidemiological associations between positive social interactions and emotion experiences and physical health outcomes in older adulthood. A neurobiological understanding of resilience can inform efforts for both prevention and intervention of diseases or problems common in later life.

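### Hypothesis 4 claims that oxytocin effects are similar across age, but the only stated inference is a test for a difference, so only a non-significant result could support it

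*Protocol article*

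**What the plan says.** Specific Aims states hypothesis 4 as "Effects of oxytocin are similar across a range of younger and older adult ages" and hypothesis 2 as "Oxytocin and social support have similar and additive stress-buffering effects". It adds that the experiment will test whether the two effects are similar and additive.

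Data Analyses repeats hypothesis 4 as "Effects of oxytocin are similar across younger and older aged adults by comparing the change in responses before and after stress". For age it names "multiple linear regression techniques incorporating an interaction term between age and oxytocin", with linear mixed models as a possible alternative. The general rule is "Statistical tests will be two-tailed and conducted at the .05 level of significance". The strategy is to fit all interactions first and then use likelihood ratio tests to move to a simpler model, which the article describes as statistically equivalent.

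For hypothesis 2 the same section changes the question to whether "Oxytocin combined with social support reduces the effects of stress more than the individual effects of oxytocin and social support". Multiplicative effects of oxytocin and support are also to be looked at graphically.

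Power and Sample Size offers, for the age analysis, "80% power to detect a medium sized effect using multiple linear regression to consider age and oxytocin". Future Directions says that the study will give solid evidence on, among other things, "whether it has similar effects regardless of age or gender". The Discussion part of the abstract says much the same for age and gender groups.

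**The concern.** Hypothesis 4 claims that a difference is absent or small. A two-sided interaction test takes no difference as its null, so a non-significant result means only that the data did not rule out zero. It does not rule out large differences either. The article gives no margin, no interval criterion and no power for showing similarity. The model-reduction step adds to the problem: once a non-significant age-by-oxytocin term is dropped, the final model shows one oxytocin effect for all ages and no estimate of how far that effect might vary.

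The incentive then runs the wrong way, because noisier data and fewer participants make hypothesis 4 look better supported. At stake is one of the four named hypotheses, and the one on which the article's message about healthy aging leans. A reader could be told that the effect holds across adulthood when the data are compatible with no effect at the older end.

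**Working it through.** **The plan's own figure.** The 80% power for age and oxytocin cannot be reproduced, because the article gives neither the numerical effect size, nor the number of predictors, nor the total sample. It is in any case power to detect an effect, not to show similarity.

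**Inputs.**
- Sample size: 40 per condition (Sample), 40 per gender/treatment group (Power and Sample Size), cells of 40 (Data Analyses). The 2 × 2 × 2 design gives 8 × 40 = 320. Four groups of 40 give 160. Both are shown.
- Age: 25 to 65 (Sample), assumed uniform, so SD = 40/√12 = 11.55 years.
- Assumed: residual SD of the change score = 1, equal allocation, normal approximation.

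**Precision for age by oxytocin.** The difference in age slope between arms has SE = 2/(SD_age × √N). Over 40 years the SE is 80/(11.55 × √N).
- N = 160: 80/(11.55 × 12.65) = 0.55, so the 95% half-width is 1.96 × 0.548 = 1.07 SD.
- N = 320: 80/(11.55 × 17.89) = 0.39, so the 95% half-width is 1.96 × 0.387 = 0.76 SD.

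Under a uniform spread the range cancels: the SE for the difference between the two ends is 2√12/√N. The lower limit of 22 given under Generalizability of Effects would therefore not change the end-to-end result.

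**Chance that the interaction test misses a true age difference D** (two-sided 5%):

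| Oxytocin effect at 25 → at 65 | D | N = 160 | N = 320 |
|---|---|---|---|
| 1.0 → 0 SD | 1.0 | 55% | 27% |
| 0.75 → 0.25 SD | 0.5 | 85% | 75% |

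In the first row the average effect is 0.5 SD. The overall oxytocin comparison has SE 2/√N = 0.158 or 0.112, hence power of about 88% or 99%. At N = 160 the more likely outcome is thus a significant overall effect with a non-significant age interaction, although the effect at 65 is nil.

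**What a similarity criterion would need.** The 90% half-width is 1.645 × 0.548 = 0.90 SD (N = 160) or 1.645 × 0.387 = 0.64 SD (N = 320). No smaller margin could be met. With a true difference of zero, the chance of showing similarity is 0% at either size for a margin of 0.5 SD, and 14% or 65% for a margin of 1.0 SD. For 80% power the total needed is about 1,645 (margin 0.5), 643 (0.8) or 412 (1.0).

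**Hypothesis 2, secondary.**
- Additivity: the oxytocin-by-support interaction has SE 4/√N = 0.316 or 0.224, so the 95% interval is ±0.62 or ±0.44 SD. A true departure of 0.5 SD is missed 65% or 39% of the time.
- Similarity: oxytocin alone versus support alone has SE √(2/40) = 0.224 or √(2/80) = 0.158, so the 95% interval is ±0.44 or ±0.31 SD.

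**The case against.** The best case for the plan has several parts.

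- **No stated reporting rule.** A reader might infer that the article commits itself to reporting non-significance as similarity. It does not say so. Calling the reduced model statistically equivalent is loose wording about model choice, and Future Directions asks neutrally "whether it has similar effects regardless of age or gender". Hypothesis 3 predicts a gender difference, so that sentence cannot be a promise of similarity. This stands, and the point is limited to what the stated analysis can support.
- **Hypothesis 2 is partly covered.** It is tempting to say that additivity is only inspected graphically. In fact the all-interactions model includes oxytocin by support and tests it; the graphs are an addition. The claim that the combination beats each component is a superiority claim, for which a difference test is right and imprecision is no help. One might also fear that a sub-additive pattern such as 0.5, 0.5 and 0.7 SD combined would pass. The 0.2 SD gain has only about 14% or 24% power per contrast (SE 0.224 or 0.158), so it would usually fail.
- **Power wording.** If medium meant f² = 0.15 on the single interaction term, the implied age shift would be about 2.7 SD. The article gives no f² and does not say that the figure refers to that term, so nothing here rests on it.
- **Margins may sit elsewhere.** An early mechanistic study with no clinical endpoint has no natural margin, and a fuller plan may give one. That is fair as to the margin itself. It does not remove the mismatch, because the article itself fixes the hypothesis, the test, the significance level, the reduction rule and the basis for power.

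**Conclusion.** The point holds for hypothesis 4. The aim asserts similarity, every stated inferential tool looks for a difference, and only non-significance could support the aim. Under the assumptions above, the interval for the 25-versus-65 difference is about ±1.07 SD (N = 160) or ±0.76 SD (N = 320), and complete loss of a 1.0 SD effect by age 65 goes undetected 55% or 27% of the time. Covariate adjustment or repeated measures could narrow these intervals; an age distribution bunched in the middle would widen them.

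The same limit applies, secondarily, to the similarity and no-interaction parts of hypothesis 2 as worded in Specific Aims. It does not reach the combined-better-than-each claim. The documents support no statement that the investigators will declare similarity from a non-significant test, only that the plan as written offers no other support for it.

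**What to change.** 1. Keep the age-by-oxytocin term in the hypothesis 4 model whatever the likelihood ratio test shows.
2. Report it as the difference in oxytocin effect between ages 25 and 65, with its confidence interval, for each key outcome.
3. Conclude that effects are similar only if the 90% interval lies within a margin fixed before unblinding. Otherwise report that no difference was detected and give the range not excluded.
4. Report the oxytocin-by-support interaction and the oxytocin-alone versus support-alone difference with intervals under the same rule. Leave the superiority question in hypothesis 2 to difference tests.
5. Qualify the solid-evidence wording in the abstract and in Future Directions to match.

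The cost is some analysis-plan text and one margin per key outcome, with no new data. The real price is a more modest conclusion: at 160 or 320 participants, similarity across age is likely to be inconclusive for any but a wide margin. If no defensible margin can be agreed, reporting the interval without a claim of similarity is enough.

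### Reducing the model by likelihood ratio tests, with no hypothesis term exempt, miscalibrates the sex-specific oxytocin effects, although the average effect and the interaction test itself hold up

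*Protocol article*

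**What the plan says.** In the protocol article, Data Analyses describes a general strategy for all hypotheses: "start by fitting a model that includes all interactions and then move to a statistically equivalent simpler model using likelihood ratio tests". It exempts no term and gives no retention threshold. The only level stated is the general one: "Statistical tests will be two-tailed and conducted at the .05 level of significance".

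Three of the four hypotheses turn on an interaction with oxytocin, in different ways:

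- **Gender.** Specific Aims states that "Effects of oxytocin are stronger in women versus men". The analysis text is "Oxytocin reduces effects of stress more for women than for men by comparing changes in responses before and after stress". This is a claim that an oxytocin x gender interaction exists.
- **Support.** Specific Aims states that "Oxytocin and social support have similar and additive stress-buffering effects", which predicts no oxytocin x support interaction. Data Analyses puts it as "Oxytocin combined with social support reduces the effects of stress more than the individual effects of oxytocin and social support" and compares all four combinations.
- **Age.** "Effects of oxytocin are similar across younger and older aged adults" is a claim that the oxytocin x age interaction is absent or small. An age-by-oxytocin term is named for the regression, but nothing says it survives the reduction.

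Power and Sample Size says that "power will be limited by hypotheses where 3-way interactions are being tested", and claims 80-90% power with 40 participants per gender/treatment group.

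**The concern.** The reduction operates on the terms the hypotheses are about. If the oxytocin x gender test is not significant, the term leaves the model, and the model then holds one oxytocin effect for both sexes. Calling that model equivalent to the larger one treats failure to reject as evidence of no difference.

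Suppose oxytocin works mainly in women, as the trial expects. Whenever the term is dropped, the fitted effect for women is too small, the fitted effect for men is too large, and the printed intervals take no account of the selection. Whenever the term is kept, it is kept because its estimate happened to be large, so its size is overstated. How oxytocin effects differ between women and men is a main question of this trial.

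**Working it through.** **Inputs from the article.** A 2 x 2 x 2 between-subjects design; two-sided 0.05; 80-90% power for a three-way interaction, read here as oxytocin x gender x time, which is oxytocin x gender on the pre-post change. The figure 40 is given per condition (Sample) and per gender/treatment group (Power and Sample Size), so both N = 320 (80 per gender-by-drug group) and N = 160 (40 per group) are shown.

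**Assumptions.** Change-score SD = 1, balanced cells, 0.05 as the retention threshold, no effect in men. The article prints no effect size, SD or reliability.

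**1. The stated power.** The 80-90% cannot be reproduced without those inputs, but the effect it implies can be computed. With n per gender-by-drug group, the SE of the difference in differences is sqrt(4/n), and the detectable interaction is (1.96 + z_power) x sqrt(4/n).

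- n = 40: 2.80 x 0.316 = 0.89 SD at 80%; 3.24 x 0.316 = 1.02 SD at 90%.
- n = 80: 2.80 x 0.224 = 0.63 SD at 80%; 3.24 x 0.224 = 0.72 SD at 90%.

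By the plan's own power, a single 0.05 test drops a real interaction of design size 10-20% of the time. At half that size the power is Φ(2.80/2 − 1.96) = 0.29 or Φ(3.24/2 − 1.96) = 0.37, so the term is dropped 63-71% of the time.

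**2. What happens when the term is dropped.** Take a true effect of 0.5 SD in women and 0 in men. The pooled effect is 0.25, which is 0.25 away from the truth in each sex. The pooled SE is sqrt(4/N).

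- N = 320: SE 0.112, half-width 1.96 x 0.112 = 0.219, less than the 0.25 error. Coverage given dropping is about Φ(1.96 − 0.25/0.112) = 39%.
- N = 160: SE 0.158, half-width 0.310. Coverage given dropping is about Φ(1.96 − 0.25/0.158) = 65%.

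**3. Expected drop rate.** Power at 0.5 SD is 0.352 (n = 40) and 0.609 (n = 80), so one test drops the term in 0.648 and 0.391 of trials. A retained three-way oxytocin x support x gender term protects the two-way term in about 5% of trials: 0.648 x 0.95 = 0.62 and 0.391 x 0.95 = 0.37. The simulation below agrees.

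**4. Simulation of the rule.** Three factors with all interactions, hierarchical backward reduction by likelihood ratio test at 0.05.

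| True effect in women | N | Term dropped | 95% CI coverage, women | False positives, men |
|---|---|---|---|---|
| 0.5 SD | 160 | 61% | 77% | 24% |
| 0.5 SD | 320 | 37% | 76% | 26% |
| 0.3-0.5 SD, range | both | about 37-77% | about 76-84% | about 14-26% |
| Powered size (0.9-1.0 SD at 160; about 0.65 SD at 320) | each | about 11-17% | about 83-86% | about 13-17% |
| Fixed full model | both | never | about 95% | about 5% |

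**5. Adding continuous age and its interactions** (2,000 runs per scenario, effects of 0.3-0.5 SD). The term is dropped in 30-69% of runs. Coverage is 79.5-85.7% in women and 77.9-86.7% in men, and false positives in men are 13.3-22.1%. The fixed model gives 94.5-95.2% coverage and 5.1-5.5% false positives. When kept, the interaction averages 0.61-0.72 for a true 0.5 and 0.45-0.48 for a true 0.3.

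**6. What stays sound.** Coverage of the average oxytocin effect is 94-96% after reduction. Its type I error under the null is 4.2-6.2%, against 4.1-5.3% in the full model. The oxytocin x gender test rejects in 4.5-5.3% of null runs.

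**The case against.** A reader might infer that everything reported from the reduced model has wrong error rates, including the first hypothesis. The figures do not support that. In a near-balanced factorial the oxytocin main effect is almost orthogonal to the interactions, so dropping them hardly moves it. The likelihood ratio test of oxytocin x gender is also the test of the third hypothesis, and it keeps its level.

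A reader might also infer that dropping the support and age terms deletes the second and fourth hypotheses. It does not. As aims, these state additivity and similarity, so dropping their terms agrees with them. The fault there is narrower: a non-significant test is allowed to stand as support.

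The remark on limited power should not be read alone. The same section claims 80-90% power, so drop rates near 60% belong to effects below the powered size. For that reason both ranges are given.

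Finally, the article does not say that a pooled effect will be reported for each sex. It says models are chosen to suit each hypothesis, and a fuller plan may settle which fit supplies which estimate. That limits the severity. It does not answer the point, because the printed rule is a positive instruction without exception, and nothing in the article says the hypothesis estimates come from the unreduced model.

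**Conclusion.** The point holds in limited form. Followed as printed, the rule miscalibrates sex-specific oxytocin effects and intervals taken from the selected model, and it exaggerates the interactions it keeps. With an effect in women of 0.3-0.5 SD, coverage falls to about 76-84% and false positives in men rise to about 14-26%. At the plan's own powered effect sizes the harm is smaller but present, at about 83-86% and 13-17%.

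By the same logic, support- and age-specific effects are exposed, but no scenario with a real support or age interaction was simulated. The average oxytocin effect and the level of the oxytocin x gender test are not impaired.

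The sizes rest on the 0.05 retention threshold, balance, unit change-score SD, no effect in men and the two readings of 40. This should be fixed, but it is not a fatal flaw.

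**What to change.** For each outcome, specify one fixed model that keeps oxytocin x support, oxytocin x gender and oxytocin x age, each with time, whatever their p-values. Report these interactions, and the sex-, support- and age-specific oxytocin effects, with 95% confidence intervals from that model. Confine likelihood ratio reduction to the covariance structure and to higher-order terms outside the four hypotheses. Delete the claim that the simpler model is statistically equivalent.

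The change is to wording only and needs no new data. Its cost is slightly wider intervals. It should be made before outcome data are analysed.
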